#### Clinical data analysis

SPSS 25.0 software will be used for data analysis. The measurement data will be normally distributed and expressed as mean ± standard deviation (
$\bar{x}$
 ± *s*). Paired *t*-test will be used for comparisons between groups before and after treatment. One-way analysis of variance will be used for the comparison of differences between the three groups, and the *q*-test will be used for comparisons between groups. The *χ*^2^-test will be used for pairwise comparisons of enumeration data, and the Mann–Whitney test and Wallis rank sum test will be used for comparisons among the three groups. *p* < 0.05 will be considered statistically significant.

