### Randomization and blinding

SPSS 25.0 software will be used to generate 117 random numbers between 0 and 1 and rank them. They will be marked and divided into 3 groups (the acupuncture for arousal group, rTMS group, and the acupuncture for arousal combined with rTMS group) and made into cards. These random cards will be placed in opaque, sealed envelopes. The patients will extract the cards according to the order of enrollment and be assigned to the corresponding groups according to the contents of the cards.

Owing to the particularity of acupuncture treatment, this study will not implement a double-blind approach and will only implement a blind evaluation of the efficacy. To reduce detection bias, this study’s efficacy evaluation will be completed by professional evaluators who are not involved in the treatment process and do not know the grouping. These evaluators are senior personnel in the field of coma rehabilitation, with standardized behavioral scale assessment certification qualifications. And before the start of the study, all evaluators will be trained and assessed in a unified manner to ensure the homogeneity of the evaluation criteria.

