### Interventions

#### Both groups

Baseline data (including stroke type, family history, and demographic information) will be collected from eligible patients. Before treatment, the GCS score and the CRS-R score will be evaluated, and S-100β, NSE, and fMRI data will be measured. The laboratory test items will be detected for safety evaluation (Table 2).

**Table 2 tab2:** Comparison of baseline characteristics among three groups (before treatment).

Category		Acupuncture for arousal group (*n* = 39)	rTMS group (*n* = 39)	Acupuncture for arousal combined with rTMS group (*n* = 39)	*p*-value
Demographics		-	-	-	-
Age (years, Mean ± SD)		XX ± XX	XX ± XX	XX ± XX	-
Gender (male/female, *n*)		XX (XX%)	XX (XX%)	XX (XX%)	-
Disease duration (days, Mean ± SD)		XX ± XX	XX ± XX	XX ± XX	-
Comorbidities (HTN/DM, etc. *n*)		XX (XX%)	XX (XX%)	XX (XX%)	-
Stroke type		-	-	-	-
Ischemic stroke (*n*)		XX (XX%)	XX (XX%)	XX (XX%)	-
Hemorrhagic stroke (*n*)		XX (XX%)	XX (XX%)	XX (XX%)	-
Severity		-	-	-	-
GCS score (3–15, Mean ± SD)		XX ± XX	XX ± XX	XX ± XX	-
CRS-R Scale	CRS-R total score (0–23, Mean ± SD)	XX ± XX	XX ± XX	XX ± XX	-
	MCS− subgroup (*n*)	XX (XX%)	XX (XX%)	XX (XX%)	-
	MCS+ subgroup (*n*)	XX (XX%)	XX (XX%)	XX (XX%)	-

Age, Disease duration, GCS score, and CRS-R total score are measurement data, and the data will be presented as “Mean ± SD.” Gender, Stroke type, and MCS subgroup are enumeration data, and the data will be presented as “*n* (%).” *p*-value: The *p*-value come from One-way analysis of variance (measurement data) or Mann–Whitney test (enumeration data). If there is no difference between the three groups, then *p* > 0.05. If there is a difference, the specific *p* is marked. HTN, Hypertension; DM, Diabetes Mellitus.

The three groups of patients will undergo basic treatment and corresponding intervention measures for 4 weeks. First, they will be given basic treatment for awakening after stroke, which mainly includes the following:

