### Sample size calculation

The GCS score was used as the primary outcome measure for the sample size calculation, following the method outlined by Lai Shilong in the Methodology of Clinical Research of Integrated Chinese and Western Medicine. Based on a study by Li Yuyuan et al. (25), the GCS score for the acupuncture combined with rTMS group was 10.30 ± 3.47 after 4 weeks of treatment. The GCS score for the acupuncture-only group was 8.33 ± 2.97, whereas that for the rTMS group was 8.16 ± 2.98. Taking *α* = 0.05, two-sided test, and *β* = 0.2, the ratio of the three groups of sample sizes was 1:1:1. After the above values are substituted with PASS 15 software, the sample size required for each group is calculated to be 32 cases. Considering a shedding rate of 20%, 39 patients are included in each group, and 117 patients are ultimately included in this study.

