#### MRI data analysis

The MRI data are preprocessed using the SPM8 software platform (SPM8, Wellcome Department of Imaging Neuroscience, London, United Kingdom). Referring to the study of resting-state connectivity of DLPFC in PSD patients (32), we select DLPFC as the seed point, use WFU Pickatlas (33) to define the region of interest (ROI) in CCN, and perform whole brain regression analysis. The resting state connectivity of DLPFC in CCN is compared among the three groups, and the brain changes of each group are evaluated by paired t-test through intra-group analysis (before and after treatment). Covariates such as age and gender are included in the data analysis. The Pearson correlation coefficient is used to analyze the relationship between the improvement of the scale and the change of fMRI image data.

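### The clinical measures are compared between arms without using their baseline values; ANCOVA would cost almost nothing and gain precision, by an amount that depends on a correlation the protocol does not give

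*Protocol article*

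**What the plan says.** Under Clinical data analysis the between-arm test is fixed: "One-way analysis of variance will be used for the comparison of differences between the three groups". For pairs of arms, the same section adds that "the *q*-test will be used for comparisons between groups". No covariate is named for any clinical outcome. The one explicit use of baseline values there is the before-after test: "Paired *t*-test will be used for comparisons between groups before and after treatment".

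The baseline values exist. Under Interventions, Both groups: "Before treatment, the GCS score and the CRS-R score will be evaluated, and S-100β, NSE, and fMRI data will be measured". Table 2 also collects MCS−/MCS+ status, stroke type and disease duration.

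Under Randomization and blinding, "SPSS 25.0 software will be used to generate 117 random numbers between 0 and 1 and rank them"; no stratification factor is mentioned. Covariates appear only under MRI data analysis: "Covariates such as age and gender are included in the data analysis".

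Under Sample size calculation, "The GCS score was used as the primary outcome measure for the sample size calculation". The inputs there are unadjusted 4-week means and SDs.

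**The concern.** The test is a stated choice, so it can be reviewed as it stands. Two consequences follow from leaving the baseline out.

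First, precision. Variation in week-4 scores that the baseline could explain stays in the error term. This matters most for the combined arm against each single treatment, the contrasts that answer the trial's question.

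Second, chance imbalance. Patients may have ischaemic or haemorrhagic stroke, be MCS− or MCS+, and have had impaired consciousness for any time under 6 months. With about 39 per arm and no stated stratification, some imbalance in baseline severity is to be expected. Table 2 plans p-values for baseline differences, but the analysis section does not say what follows if one is found.

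**Working it through.** **Inputs** (Sample size calculation): GCS after 4 weeks 10.30 ± 3.47 (combined), 8.33 ± 2.97 (acupuncture), 8.16 ± 2.98 (rTMS); two-sided alpha 0.05; power 80%; 32 per arm, 39 after a 20% allowance for loss. No baseline-to-week-4 correlation is given, so rho is assumed over 0.2 to 0.7.

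**1. The plan's own figure.** One-way ANOVA with three arms has noncentrality λ = n·Σ(mᵢ − m̄)²/SD². The grand mean is 8.93 and Σ(mᵢ − m̄)² = 1.37² + 0.60² + 0.77² = 2.83.
- SD 2.97: λ = 32 × 2.83/8.82 = 10.27, power 81%; at n = 31, 79.9%. So 32 per arm is reproduced with the SD of a single-treatment arm (2.98 also gives 32).
- Root-mean-square SD of the three arms, √[(3.47² + 2.97² + 2.98²)/3] = 3.149: 35 per arm are needed. Power is 76.3% at n = 32 and 84.7% at n = 39.

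**2. Combined versus acupuncture, unadjusted.** The difference is 10.30 − 8.33 = 1.97 and the two-arm SD is √[(3.47² + 2.97²)/2] = 3.23. The noncentrality of the t-test is 1.97/(3.23·√(2/n)).
- n = 39: 2.69, power 75.8%.
- n = 32: 2.44, power 67.1%.

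For combined versus rTMS (difference 2.14) the powers are 82.2% and 74.1%.

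**3. With baseline adjustment.** ANCOVA replaces SD by SD·√(1 − rho²), so residual variance falls by rho²: 4%, 9%, 25% and 49% at rho 0.2, 0.3, 0.5 and 0.7.

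| rho (assumed) | Combined vs acupuncture, n = 39 | n = 32 | Omnibus, n = 39 | n = 32 |
|---|---|---|---|---|
| 0 (unadjusted) | 76% | 67% | 85% | 76% |
| 0.2 | 78% | 69% | 86% | 78% |
| 0.3 | 80% | 71% | 88% | 80% |
| 0.5 | 87% | 79% | 94% | 88% |
| 0.7 | 96% | 92% | 99% | 97% |

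The lowest rho giving 80% for combined versus acupuncture is about 0.32 at n = 39 and 0.52 at n = 32.

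Simulating the q-test (Student-Newman-Keuls form, 40,000 runs), the chance that both combined-arm contrasts are significant at n = 39 is 69%, 74%, 83% and 95% for rho 0, 0.3, 0.5 and 0.7. At n = 32 it is 58%, 63%, 73% and 90%.

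**4. Chance imbalance.** The standard error of a baseline difference between two arms of 39 is √(2/39) = 0.226 SD. With equal baseline and week-4 SDs the slope equals rho, so a one-standard-error imbalance at rho 0.5 and SD 3.15 shifts the unadjusted difference by 0.5 × 0.226 × 3.15 = 0.36 points. That is 18% of the planned 1.97. At rho 0.3 the shift is 0.21 points, or 11%.

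**5. If change scores are meant.** With equal SDs, variance relative to unadjusted week-4 scores is 2(1 − rho) for change scores and 1 − rho² for ANCOVA: 1.40 against 0.91 at rho 0.3, 1.00 against 0.75 at rho 0.5, and 0.60 against 0.51 at rho 0.7. ANCOVA is better at each value.

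**The case against.** The strongest reply is that nothing here is an error. In a randomised trial, a one-way ANOVA of post-treatment values is unbiased and holds its type I error, and the sample size was set on unadjusted scores, so design and test agree. That stands: this is an efficiency point.

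A reader might infer that adjustment would recover all the power the trial lacks. The protocol does not support that. Rho is not given, and entry restricted to MCS narrows the baseline range and may lower it. At n = 32 and rho 0.3 the weaker contrast reaches only 71%. Nor is the omnibus test short of power at 39 per arm. Using 39 also leans on the planned intention-to-treat analysis with last observation carried forward. A carried-forward value may be the baseline itself, which would alter the correlation assumed.

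A reader might also infer that a baseline difference passes in full into the effect, or that adjustment removes all chance imbalance. Only slope times imbalance passes through, and adjustment acts on the covariates in the model and on others only as far as they correlate with them.

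The point does not cover every outcome: awakening time and awakening rate have no baseline value of their own. The wording on differences between the groups could mean change scores, which would already use the baseline; step 5 shows that ANCOVA remains the better choice. Finally, the protocol gives no distributions that would justify log-transforming S-100B or NSE, and it already provides a non-parametric alternative if assumptions fail.

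**Conclusion.** The point holds as a nearly free improvement for GCS, CRS-R, S-100B and NSE; the planned test is not invalid. For combined versus acupuncture on GCS, baseline adjustment adds about 2 to 20 percentage points of power at 39 per arm and about 2 to 25 at 32, for rho from 0.2 to 0.7. It also takes out the part of the estimate due to imbalance in the baseline score. These figures rest on the protocol's planning means and SDs, on an assumed rho, on a linear baseline relation with a common slope and, for n = 39, on imputed values behaving like observed ones. At low rho the gain is small, but so is the cost.

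**What to change.** Replace the one-way ANOVA for GCS, CRS-R, S-100B and NSE by ANCOVA of the week-4 value on arm and the baseline value of the same measure. One or two further covariates already collected, such as MCS−/MCS+ status or disease duration, may be added if named in advance. MCS status is derived from the CRS-R, so it overlaps with baseline CRS-R. Report adjusted differences with 95% confidence intervals for combined versus acupuncture and combined versus rTMS, and state the rho assumed and the power it implies. Keep a fallback for violated assumptions.

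The cost is a change of analysis wording and one degree of freedom per continuous or two-level covariate. No new data are needed. The model should be fixed before outcome data are seen, so that covariates are not chosen afterwards.

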### Efficacy evaluation

#### The threshold of clinical improvement (Using the CRS-R scale as the reference standard)

Using the type of disturbance of consciousness in the CRS-R scale as the reference threshold for clinical improvement. The clinical significantly effective: Patients initially diagnosed with either MCS− or MCS+ who progress to eMCS following therapeutic intervention. The clinical effective: Patients initially diagnosed with MCS− who progress to MCS+ status following therapeutic intervention. The clinical ineffective: Characterized by either (a) patients initially diagnosed with MCS− who regress to vegetative state (VS) or maintain MCS− status following therapeutic intervention; or (b) patients initially diagnosed with MCS+ who regress to VS, MCS-, or maintain MCS+ status without further progression following therapeutic intervention.

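### Tests for categorical data are mis-assigned (Mann–Whitney for three groups), the pairwise chi-square tests have no gate or adjustment, and baseline MCS−/MCS+ is ignored

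*Protocol article*

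**What the plan says.** - **Three-group step (Clinical data analysis).** "the Mann–Whitney test and Wallis rank sum test will be used for comparisons among the three groups".
- **Pairwise step (same sentence).** The chi-square test "will be used for pairwise comparisons of enumeration data".
- **Threshold (same section).** A p-value below "0.05 will be considered statistically significant". This is a per-test level; no family-wise rate is given. Continuous data get one-way ANOVA across the three groups and the q-test for comparisons between groups.
- **Table 2 footnote.** The single p-value column compares three groups, and its source is given as "One-way analysis of variance (measurement data) or Mann–Whitney test (enumeration data"). The footnote lists gender, stroke type and MCS subgroup as enumeration data. Kruskal–Wallis and chi-square are not mentioned there.
- **Efficacy grade (threshold of clinical improvement).** The middle grade, *effective*, is defined only for MCS− patients "who progress to MCS+ status following therapeutic intervention". An MCS+ patient who reaches eMCS is *significantly effective*; any other outcome is *ineffective*.
- **Awakening effective rate.** An MCS− patient counts as awakened on reaching MCS+ or eMCS, an MCS+ patient only on reaching eMCS.
- **Randomization and blinding.** Ranked random numbers are split into three groups, with no stratification. Covariates are named only for the MRI analysis.

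**The concern.** There are three problems.

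1. **The test does not fit the comparison.** A two-sample test cannot produce a three-group p-value, so the Table 2 p-values for gender, stroke type and MCS subgroup cannot be obtained as described. Chi-square, which handles three groups directly, is assigned only to pairs. The two roles look swapped.
2. **The pairwise categorical tests have no stated error control.** The q-test is a multiple-comparison procedure, so the continuous endpoints have some protection. The awakening rate is binary and falls under the chi-square sentence, which names no adjustment and no prior overall test. It is one of the results that clinical readers will take up most easily.
3. **Baseline category drives both CRS-R endpoints.** The two strata face different hurdles. A chance excess of MCS− patients in one arm can therefore move that arm's awakening rate and grade distribution without any treatment effect.

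Left as it is, the choice of overall test, and of whether pairwise results depend on it, could be made after the data are seen.

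**Working it through.** **Inputs.** Three arms of 39 (Sample size calculation; all randomised patients are analysed under ITT with LOCF). Per-test level 0.05. The protocol gives no awakening rate, so a common rate under the null is assumed and varied from 0.1 to 0.7.

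**The plan's own figure.** No family-wise error rate is stated, so there is none to reproduce. The sample size only supplies n. With GCS means 10.30, 8.33 and 8.16, one-way ANOVA at alpha 0.05 and a common SD of 2.97 needs 32 per group (power 0.813). Then 32 × 1.2 = 38.4, rounded up to 39.

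**Step 1: is an overall test available?** Yes. On a binary outcome the Kruskal–Wallis statistic equals (N − 1)/N times the Pearson 3×2 chi-square. With N = 117 the factor is 116/117 = 0.991, so Kruskal–Wallis is a valid three-group test of the awakening rate. It also uses the order of the efficacy grade. Mann–Whitney has no three-group form.

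**Step 2: large-sample error of three ungated tests.** At least one pair is significant when the range of three standard normals exceeds 1.96 × √2 = 2.772. The studentized range distribution for three groups gives 0.122. Treating the tests as independent would give 1 − 0.95³ = 0.143, which is too high because the pairs share arms. For the two contrasts with the combined arm only, the simulated value is 0.091.

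**Step 3: exact error at 39 per arm.** All three-arm binomial outcomes were enumerated at each common rate. Values are the percentage chance of at least one p < 0.05.

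| Common rate | Any of 3, uncorrected | 2 contrasts with combined arm, uncorrected | 3 tests gated on Kruskal–Wallis | Any of 3, Yates |
|---|---|---|---|---|
| 0.1 | 14.0 | 10.5 | 4.4 | 3.6 |
| 0.2 | 12.2 | 9.2 | 4.8 | 6.6 |
| 0.3 | 12.9 | 9.6 | 4.9 | 7.0 |
| 0.4 | 12.3 | 9.2 | 4.9 | 7.2 |
| 0.5 | 13.0 | 9.7 | 5.2 | 7.8 |
| 0.6 | 12.3 | 9.2 | 4.9 | 7.2 |
| 0.7 | 12.9 | 9.6 | 4.9 | 7.0 |

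With 32 per arm the first result column becomes 12.1–14.4. A Pearson 3×2 gate at 39 per arm cannot exceed its own size, 4.6–5.2. Bonferroni at 0.05/3 gives 3.5–4.5.

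**Step 4: why the gate is enough with three groups.** If all three rates are equal, a false pairwise claim needs a false overall result, which has about a 5% chance. If only two are equal, there is one true pairwise null, and it is tested at 0.05.

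**Step 5: baseline category.** Let q be an arm's share of MCS− patients, and let a and b be the awakening probabilities of MCS− and MCS+ patients. The arm's rate is qa + (1 − q)b. A difference d in q between two arms shifts the comparison by d(a − b) with no treatment effect. The share graded *effective* is q times the probability of moving from MCS− to exactly MCS+; MCS+ patients add nothing. The protocol gives neither a nor b, so the shift cannot be sized.

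**The case against.** A reader might infer that the awakening rate goes straight to pairwise tests with no overall test. The text does not say so. The sentence that lists Mann–Whitney also names the Wallis test, and neither order nor gating is stated. The sentence may even condense a sensible scheme: Kruskal–Wallis overall, Mann–Whitney for pairs. An article often leaves such details to a fuller document. This removes the stronger reading but not the point: the wording assigns Mann–Whitney to the three-group comparison, and the Table 2 footnote names it alone, so the condensed-scheme reading cannot rescue the footnote.

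A reader might also take 12–13% as the trial's actual error set against a promised 5%. That is not supported either. The protocol's 0.05 is a per-test threshold. The figure needs no gate, all three contrasts counted and an uncorrected chi-square; with Yates correction it is 3.6–7.8%.

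On baseline category, one can fairly answer that randomisation already allows for chance imbalance within the nominal error rate, that the awakening rate counts improvement from either stratum, and that Table 2 will show the MCS−/MCS+ counts. This stands: the unstratified comparison is not invalid. Stratifying is an improvement that uses data already collected, not the repair of a biased test.

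**Conclusion.** The point holds in three parts of unequal strength.

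- **Certain.** Mann–Whitney is wrongly named for three-group comparisons in Clinical data analysis and in the Table 2 footnote.
- **Conditional.** The pairwise chi-square tests are neither gated nor adjusted in the text. If all three are run ungated and uncorrected, the chance of at least one false positive on the awakening rate is about 12–13%, assuming 39 per arm and a common rate of 20–70%. It is about 9–10% for the two contrasts with the combined arm, and about 4–5% if the tests follow a significant overall test.
- **An improvement.** Baseline MCS category affects which grade is reachable and what counts as awakening, and the clinical analysis takes no account of it. No size can be given.

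This should be corrected before results are seen. It does not undermine the design.

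**What to change.** 1. In Clinical data analysis and the Table 2 footnote, remove Mann–Whitney as a three-group test. For binary and nominal data, name the overall three-group chi-square (an exact test if cells are sparse). For the ordered efficacy grade, name Kruskal–Wallis.
2. State that pairwise tests are run only if the overall test is significant at 0.05.
3. For the awakening rate and the efficacy grade, make the analysis stratified by baseline MCS−/MCS+ with Cochran–Mantel–Haenszel tests: overall across the three arms first, using the ordered form for the grade, then pairwise on the same gate. Say that this stratified version is the main analysis of these two endpoints, so that it does not compete with the unstratified tests in item 1.

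The cost is wording only: no change to recruitment, assessments or data collected, since the MCS subgroup is already recorded at baseline. The downside is that a pairwise difference can be claimed only after a significant overall test.

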#### MRI data analysis

The MRI data are preprocessed using the SPM8 software platform (SPM8, Wellcome Department of Imaging Neuroscience, London, United Kingdom). Referring to the study of resting-state connectivity of DLPFC in PSD patients (32), we select DLPFC as the seed point, use WFU Pickatlas (33) to define the region of interest (ROI) in CCN, and perform whole brain regression analysis. The resting state connectivity of DLPFC in CCN is compared among the three groups, and the brain changes of each group are evaluated by paired t-test through intra-group analysis (before and after treatment). Covariates such as age and gender are included in the data analysis. The Pearson correlation coefficient is used to analyze the relationship between the improvement of the scale and the change of fMRI image data.

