**Methods and analysis:**

This is a single-center design, randomized, controlled, third-party blind trial involving 117 patients. Three groups of patients will receive 4 weeks of treatment. Under basic treatment, the acupuncture for arousal group will only receive acupuncture treatment. The rTMS group only receives rTMS treatment; the combined group is treated with the acupuncture for arousal and rTMS. The main outcome indicators are the GCS score scale, the CRS-R score scale, central nerve-specific protein (S-100B), neuron-specific enolase (NSE), and functional magnetic resonance imaging (fMRI). The secondary outcome indicators are laboratory safety parameters, including routine blood tests, routine urine tests, coagulation tests, electrocardiograms, liver function tests, and renal function tests. Finally, the measurement data and enumeration data will be analyzed via SPSS 25.0 software.

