##### Functional magnetic resonance imaging

Functional magnetic resonance imaging (fMRI) can reflect the changes in blood oxygenation (BOLD), blood flow changes, and other conditions in the functional areas of the brain and then evaluate brain function stereoscopically and intuitively. BOLD-fMRI imaging can reflect dynamic changes in the functional activity of the cerebral cortex through hemodynamic changes following neuronal activity. A 3.0 T superconducting magnetic resonance imaging system (Siemens) will be used to collect imaging data. The gradient echo plane imaging sequence will be used to collect BOLD-fMRI data. Resting-state functional MRI is acquired at the beginning of the scan, and the parameters are as follows: TR = 2,000 ms, TE = 30 ms, flip angle = 90°, FOV = 224 × 224 mm, matrix size = 64 × 64 mm, slice thickness = 3.5 mm, and slice number = 33 slices. BOLD-fMRI will be performed 30 min before the intervention (baseline period) and 30 min after the end of the 4-week intervention (end period).

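### fMRI is a main outcome, but its analysis is spread over several tests with no deciding quantity or between-arm contrast, and the within-arm tests among them do not compare treatments

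*Protocol article*

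**What the plan says.** The abstract's methods paragraph lists, after the GCS and CRS-R, "central nerve-specific protein (S-100B), neuron-specific enolase (NSE), and functional magnetic resonance imaging (fMRI") as main outcome indicators, and the fMRI subsection stands under Primary outcomes. That subsection gives scan parameters and two scan times, before the intervention and after its four weeks, but no outcome variable.

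The MRI data analysis section takes the DLPFC as seed and plans four kinds of analysis:

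- a seed-based step: "define the region of interest (ROI) in CCN, and perform whole brain regression analysis";
- a between-arm comparison: "The resting state connectivity of DLPFC in CCN is compared among the three groups";
- within-arm tests: "the brain changes of each group are evaluated by paired t-test through intra-group analysis (before and after treatment");
- Pearson correlations, used to "analyze the relationship between the improvement of the scale and the change of fMRI image data".

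Age and gender are given as examples of covariates; baseline connectivity is not mentioned. No analysis is named as deciding and none is labelled exploratory. The section gives no significance threshold. The significance rule for analyses, p "< 0.05 will be considered statistically significant", closes the clinical data analysis section.

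**The concern.** A main outcome should come down to one quantity and one treatment contrast, so that it is clear beforehand what would count as a positive or a negative result. Here a reader cannot tell whether the fMRI outcome is one value per patient or a map, nor which of the four kinds of analysis settles it. This multiplicity lies inside the fMRI outcome, so dividing alpha over the five named main outcomes would not remove it.

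The within-arm paired tests add a second problem. Patients have had impaired consciousness for less than six months and all receive the basic treatment, so connectivity may change in any arm without a specific effect of acupuncture or rTMS. A significant change in the combined arm beside a non-significant one in a single-treatment arm is also not evidence that the arms differ. The risk of such a reading is real: the Discussion takes a fall in NSE and S-100B from baseline as a sign of therapeutic effect. At stake is the mechanistic claim about brain reorganisation that the Introduction promises from these scans.

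**Working it through.** The article states no error rate, threshold or sample size for fMRI, so there is no fMRI figure to reproduce. The stated 32 evaluable patients per group were calculated for the GCS and do not bear on this point.

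**Inputs from the article.** Three arms, one paired test each; one three-group comparison; two scales (GCS, CRS-R) available for correlation; level 0.05 ("0.05 will be considered statistically significant"); image grid "FOV = 224 × 224 mm, matrix size = 64 × 64 mm, slice thickness = 3.5 mm, and slice number = 33 slices", with the matrix taken as 64 × 64 samples.

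**Assumed, not in the article.** Brain volume 1,000–1,500 mL; smoothing 6, 8 or 12 mm FWHM; independence of tests where stated.

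**What each analysis answers.** Only the three-group comparison uses the randomisation to compare treatments. The paired tests ask whether an arm changed over four weeks. The correlations ask whether scale change and connectivity change go together. The regression yields the connectivity, or a map of it.

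**One value per patient, each test at 0.05, no true effect:**

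- one deciding between-arm test: 5%;
- three within-arm tests: 1 − 0.95^3 = 14.3%;
- these plus the three-group test: 1 − 0.95^4 = 18.5%;
- these plus one correlation per scale: 1 − 0.95^6 = 26.5%.

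The arms hold different patients, so the three within-arm tests are independent of one another. Dependence of the three-group test on them can therefore only move the 18.5% between 14.3% and 14.3% + 5% = 19.3%.

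**Voxelwise testing, conditional on uncorrected p < 0.05.** In-plane size is 224/64 = 3.5 mm and slices are 3.5 mm, so a voxel is 3.5^3 = 42.875 mm³.

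- 1,000 mL: 1,000,000/42.875 ≈ 23,300 voxels; × 0.05 ≈ 1,170 false-positive voxels per null map.
- 1,500 mL: 1,500,000/42.875 ≈ 35,000 voxels; × 0.05 ≈ 1,750.

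Null paired-difference maps were simulated with 32 patients, about 28,000 voxels and 60 maps per smoothness:

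| FWHM | Maps with any voxel at 0.05 | Median largest cluster at 0.05 | Maps with a cluster of 10 or more voxels at 0.001 |
|---|---|---|---|
| 6 mm | 60 of 60 | 25 voxels | 0% |
| 8 mm | 60 of 60 | 53 voxels | 5% |
| 12 mm | 60 of 60 | 124 voxels | 40% |

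At uncorrected 0.001 every map still had at least one voxel (mean about 27). The voxelwise error rate therefore depends heavily on a rule that the article does not state.

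**The case against.** A reader might infer that some brain region is bound to come out significant by chance and that the imaging outcome cannot be negative. The document does not support this. It needs uncorrected voxelwise testing at 0.05, which is stated nowhere: the 0.05 rule belongs to the section on clinical data in SPSS, while MRI has its own section and software. Voxel or cluster correction is a detail that an article may leave to the full protocol or analysis plan, so silence on it is not a fault. This part of the objection stands.

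The analysis is also not only a whole-brain search. The randomised comparison is planned, with a named seed and confined to a network. The whole-brain regression can be read as the per-patient step that produces seed connectivity. The general statistical section treats fMRI as repeated-measurement data with a Greenhouse–Geisser correction, which fits one summary value per patient. These readings are fair, and they are why the size is given first at one value per patient. They do not settle the matter. With only two scans per patient sphericity cannot fail, so that sentence does not identify the measure, and the three-group comparison is still not named as deciding.

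Finally, the trial is sized on the GCS, and imaging is described largely as serving the study of mechanism. That limits the consequence, but the text still lists fMRI as primary. Mean seed-to-network connectivity is one defensible summary among several; what matters is that one is fixed in advance.

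**Conclusion.** The point holds in limited form. A main outcome is left without a deciding quantity or contrast, although the section is detailed enough to give seed, atlas, software and tests. Three of the planned tests do not compare treatments. At one value per patient, the chance of at least one false positive over the three within-arm tests and the three-group test is about 18.5% (independence assumed; 14.3% to 19.3% whatever the dependence of the fourth test), against 5% for a single deciding test. This supposes no change in any arm; recovery common to all arms would make significant within-arm results more frequent without any treatment difference.

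That a false region is almost certain may be said only under the condition that voxels are tested at 0.05 without correction. The figures for that case also rest on assumed brain volume and smoothing, and they are not properties of the plan as written.

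**What to change.** In the MRI data analysis section:

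- Let the between-arm comparison already planned decide the fMRI outcome, on one pre-set value per patient, for example mean connectivity of the DLPFC seed (side stated) within the fixed CCN mask at the end of treatment.
- Compare the combined arm with each single-treatment arm, adjusting for the baseline value of the same measure as well as age and gender.
- State whether both contrasts must succeed, each at 0.05, or whether either suffices, in which case 0.025 each keeps the total at 5%.
- Label the whole-brain regression, the within-arm paired t-tests and the scale correlations exploratory.
- Show any map only with family-wise voxel or cluster correction.

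The change is one of wording, with the same scans and software. The cost is that fewer regions can be reported as significant.
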